### Interventions

2.7

The trial will start with a 1-week screening period, during which other TCM medications for CAD are discontinued. Subsequently, all participants will take DLT or placebo for 4 weeks. Both groups continue routine medications, including long-acting nitrate drugs, lipid lowering drugs, and anti-platelet drugs. Cornell Chemical Company, who produces DLT and DLT placebo (both 0.3 g × 15 tablets, 5 tablets at a time, 3 times per day), guarantees that DLT (batch number, 20190905) and DLT placebo (batch number, 20190801S) have the same package, color, shape, and taste. DLT is manufactured according to the standards of the Pharmacopoeia of the People's Republic of China (version 2015). The placebo consists of starch, dextrin, and food coloring (mass ratio, 2:1:0.006). The drug counter will be locked and stored at room temperature under the management of a drug manager. In week 0 and week 2, researchers will hand out the drugs, according to the group numbers generated by CRS. All participants will be invited to a WeChat group, and a researcher will send messages every morning to remind patients to take the medicine. We will record and evaluate the administration of drugs in 2 ways.

(1)We will send an “angina treatment diary” in the form of a questionnaire (see Fig. 2) to the WeChat group every night, and the participants have to upload a picture of the medicines taken that day.(2)In week 2 and week 4, the drugs that the participants have received, taken, and returned will be recorded in CRFs.

**Figure 2 F2:**
[figure not shown]
The interface of angina treatment diary in WeChat. (A, B) Main interface, (C) Angina number today.

### Data collection

2.8

#### Primary and secondary outcomes

2.8.1

All participants will be required to record the frequency, severity, and duration of angina in the “angina treatment diary.” The “angina pectoris diary” will be presented in the form of an electronic questionnaire, which will be sent to the patients every night via WeChat. The primary outcome is the change in the frequency of angina attacks from baseline to week 4. Secondary outcomes include the severity and duration of angina attacks, TCM efficacy, the withdrawal rate of emergency medications, blood lipid efficacy, and ECG efficacy. The severity of angina will be reported on the basis of the Visual Analogue Scale and the Canadian Cardiovascular Society score (1–2 points, only chest distress, no chest pain; 3–4 points, presence of angina during strenuous ordinary activity; 5–6 points, presence of angina during ordinary activities after meals, in the cold, in the wind, under emotional stress, or during the first few hours after waking up; 7–8 points, having difficulties walking 1 or 2 blocks or climbing one flight of stairs, at normal pace and under normal conditions; 9 to 10 points, no exertion needed to trigger angina). Angina duration refers to the time between the initial onset of symptoms to the time of remission. TCM efficacy is reported on the basis of the Curative Effect of Traditional Chinese Medicine on Coronary Heart Disease Stable Angina issued in 2018.^[30]^ The withdrawal rate of emergency drugs is calculated as follows: withdrawal rate = (number of tablets before treatment − number of tablets after treatment)/(number of tablets before treatment) × 100%. Emergency drugs mainly include nitroglycerin and the SuxiaoJiuxin Pill (another common emergency medicine in China). Blood lipids refer to total cholesterol, triglyceride, low-density lipoprotein–cholesterol, and high-density lipoprotein–cholesterol levels. The ECG efficacy standards are based on the Evaluation Criteria for Efficacy of Coronary Heart Disease Angina Pectoris and ECG (see Table 2). Among these indicators, the angina-related outcomes are derived from the electronic “angina treatment diary,” and other indicators are derived from the CRF. The data collection schedule is shown in Table 3.

**Table 2 T2:** ECG efficacy criteria.

Criteria	ECG changes
Marked effect	The ECG returns to “substantially normal” or reaches “normal ECG.”
Validation	The decrease of ST segment is to increase by more than 0.05 mV after treatment, but it does not reach the normal level. In the main electrocardiographic lead, the T wave changes lighter (up to 25%); or the T wave changes from flat to upright, improvement of atrioventricular or ventricular block.
Invalidation	The ECG is basically the same as before treatment.
Aggravation	The ST segment is to decrease by more than 0.05 mV after treatment. In the main electrocardiographic lead, the T wave changes deeper (up to 25%); or the T wave changes from upright to flat, or the upright T wave becomes inverted, and an ectopic rhythm, atrioventricular or ventricular block.

**Table 3 T3:** Schedule of data collection.

	Screening stage		Inclusion day	Treatment period	
Items	-7th Day	-1th Day	0th Day	2th Week	4th Week
Informed consent	√				
Inclusion/exclusion criteria			√		
Demographic data	√				
General clinical data	√				
Anginal frequency			√	√	√
Anginal severity and duration			√	√	√
TCM effect			√	√	√
Electrocardiograph			√		√
Blood Lipid		√			√
Vital signs		√			√
Blood pressure		√			√
Blood and urine routine		√			√
Stool routine and occult blood		√			√
Liver and renal function		√			√
Record adverse events				√	√

Checked boxes indicate the indices tested during a specific time period. General clinical data include medical history, course of the disease, treatment history, concomitant diseases, and concomitant medications. Vital signs include body temperature, respiration rate, heart rate, and blood pressure. CRF = case report form, TCM = traditional Chinese medicine.

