### Inclusion criteria

2.3

The inclusion criteria are the following:

(1)patients diagnosed with SAP with “intermingled phlegm and blood stasis syndrome;”(2)age ranging from 30 to 75 years;(3)voluntary participation;(4)using WeChat.

In respect of the diagnosis of SAP, we refer to the 2019 European Society of Cardiology Guidelines for the Diagnosis and Management of Chronic Coronary Syndromes,^[6]^ the Society for Cardiovascular Angiography and Interventions/American College of Cardiology/American Heart Association Expert Consensus Document: 2014 Update on Percutaneous Coronary Intervention Without On-Site Surgical Backup.^[28]^ Participants with a pre-test probability of >15% are recommended to undergo a coronary dual-source CT angiography. Based on the CT angiography results, patients are diagnosed with SAP in the case of at least 1 major coronary branch stenosis of more than 50%. Participants should also have typical SAP symptoms.

In respect of the diagnosis of “intermingled phlegm and blood stasis syndrome,” we refer to the Diagnostic Criteria for Syndrome Elements of Coronary Heart Disease Angina published by the Chinese Society of Traditional Chinese Medicine Cardiovascular Disease Branch in 2018.^[29]^ Syndrome elements are the smallest diagnostic units for the diagnosis of traditional Chinese medicine (TCM) syndromes. A diagnosis of “phlegm syndrome” and “blood stasis syndrome” is made if the summed scores of single syndrome elements ≥8 points. When the criteria of both syndromes are met, the “intermingled phlegm and blood stasis syndrome” is diagnosed.

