### Statistical analysis

2.16

Statistical analyses consist of 3 parts—baseline comparability analysis, efficacy analysis, and security analysis. An independent statistician will be in charge of the analyses, and Statistical Analysis System (version 9.2) will be used. All tests are 2-sided, and *P* < .05 is considered to indicate statistical significance. According to the intention-to-treat principle,^[32]^ there will be 3 analysis sets: the full analysis set, the per-protocol analysis set, and the safety analysis set. Participants who insist in taking medication for 2 weeks will be involved in the full analysis set group; if a critical variable is missing in any given case, the statistician will consider the last observation result as the final data. Patients who conform to the treatment plan will be included in the per-protocol analysis set group. The Mantel–Haenszel Chi-squared test and analysis of covariance will be conducted in the case of important baseline non-comparability. Normally distributed quantitative data will be presented as mean ± standard deviation and analyzed by Student *t* test. Non-normally distributed quantitative data will be presented as median and interquartile range and analyzed by the Kruskal–Wallis test. Ordinal data, like ECG efficacy, will be analyzed by the Kruskal–Wallis test. Qualitative data will be presented as percentage and rate and analyzed by the Chi-square test and Fisher exact test. The paired Student *t* test will be used to analyze significant differences between pre- and post-treatment. Moreover, subgroup analysis will be conducted according to gender, age, and complications to explore the internal consistency of the conclusions. For the safety analysis, the statistician will adopt the safety analysis set to evaluate the incidence rate of AEs and the change of laboratory indices. Both AEs and laboratory indices are described in lists and analyzed by the chi-square test or Student *t* test.

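### The emergency-drug withdrawal rate is undefined for participants who used none before treatment and unstable for light users; compare week-4 use adjusted for baseline instead

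*Protocol article*

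**What the plan says.** **Withdrawal rate.** Section 2.8.1 lists it as a secondary outcome and prints the formula: tablets before treatment minus tablets after, over tablets before, times 100%. The part that matters is the denominator: "number of tablets after treatment)/(number of tablets before treatment"). On the products counted it says: "Emergency drugs mainly include nitroglycerin and the SuxiaoJiuxin Pill".

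**Eligibility.** Section 2.3 asks for the diagnosis of stable angina with the TCM syndrome, and then "2)age ranging from 30 to 75 years;(3)voluntary participation;(4)using WeChat". The diagnosis rests on CT, "patients are diagnosed with SAP in the case of at least 1 major coronary branch stenosis of more than 50"%, together with typical symptoms. Neither Section 2.3 nor the exclusions in Section 2.4 set a minimum for emergency-drug use or attack count, or ask for an abnormal ECG.

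**Severity and duration.** The lowest printed severity band is "1–2 points, only chest distress, no chest pain". Duration is the time from onset to remission of an attack.

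**ECG efficacy.** In Table 2 the top category, *Marked effect*, includes reaching a normal ECG. The category *Invalidation* reads "The ECG is basically the same as before treatment".

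**Missing data.** Under Section 2.16, if a critical variable is missing, "the statistician will consider the last observation result as the final data".

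**The concern.** A ratio to baseline has a value only for participants with something to reduce. Here the denominator may be zero, and no rule covers that case. Three consequences follow if the rate is computed per participant:

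- Non-users at baseline drop out of the comparison or receive an improvised value.
- A participant who starts to need emergency drugs during the trial, which is a deterioration, has no score.
- The scale is capped at +100% and has no lower limit, so a few light users can drive a mean.

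The formula is printed in the protocol, so this is a definition that has been fixed badly and not a detail left to an analysis plan.

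Severity, duration and ECG efficacy raise a milder version of the same question: what score does a participant get who has no attack to rate, or no ECG abnormality to improve?

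**Working it through.** The protocol reports no figure for this outcome, so there is none to reproduce. The check evaluates the printed definitions.

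**1. The formula at zero and small baselines.** Rate = (before - after)/before × 100%.

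| Before | After | Rate |
|---|---|---|
| 0 | 0 | 0/0, undefined |
| 0 | 3 | -3/0, undefined |
| 1 | 4 | (1 - 4)/1 = -300% |
| 10 | 13 | (10 - 13)/10 = -30% |
| 1 | 0 | (1 - 0)/1 = 100% |
| 10 | 9 | (10 - 9)/10 = 10% |

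The same rise of three tablets, and the same fall of one, differ tenfold according to the baseline.

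**2. Do other rules in the protocol repair this?** Carrying the last observation forward does not, because the denominator is itself zero. The Kruskal–Wallis test, which Section 2.16 provides for non-normal data, would limit the pull of extreme values but cannot rank an undefined one.

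**3. Size of the loss.** Section 2.1 gives 76 participants at 1:1, so 76/2 = 38 per arm. The share f of baseline non-users is not stated and is assumed here. Evaluable per arm = 38(1 - f). With the same SD, the standard error is multiplied by 1/√(1 - f).

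| f (assumed) | Evaluable per arm | SE factor |
|---|---|---|
| 10% | 34.2 | 1.05 |
| 20% | 30.4 | 1.12 |
| 30% | 26.6 | 1.20 |
| 50% | 19.0 | 1.41 |

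These counts are before any dropout.

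**4. Attack-free weeks.** The only inputs are the previous study's weekly frequencies in Section 2.11: 1.90 ± 0.45 (treatment) and 2.55 ± 1.03 (reference).

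- Poisson counts (assumption): exp(-1.90) = 15.0% and exp(-2.55) = 7.8%.
- Normal curve with the stated SDs, taking a value below 0.5 as no attack: z = (0.5 - 1.90)/0.45 = -3.11, giving 0.1%; z = (0.5 - 2.55)/1.03 = -1.99, giving 2.3%.

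A Poisson count would have SDs of √1.90 = 1.38 and √2.55 = 1.60, both wider than those stated. The share therefore runs from near 0 to about 15%, and which arm has more attack-free weeks depends on the assumption.

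**5. ECG.** For an ECG that is normal at both visits, *Invalidation* applies because nothing has changed. *Marked effect* applies arguably, because the final ECG is normal. These are the third and first of four ordered categories, and Section 2.16 tests that order by Kruskal–Wallis.

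**The case against.** **Group totals.** Section 2.8.1 does not say whether the rate is per participant or per arm. A ratio of arm totals would avoid a zero denominator in practice. It yields one number per arm, however, and leaves no participant-level value for the tests in Section 2.16.

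**Randomisation is preserved.** Leaving out baseline non-users conditions on something measured before treatment, so those who remain are still a randomised comparison. This stands: for the withdrawal rate the cost is precision and the inability to score new use, not selection bias.

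**Summing two products.** A reader might infer that nitroglycerin and SuxiaoJiuxin units are added together. The diary described in Section 2.10 has a single item for both, which makes this plausible, but the protocol does not state it.

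**Attack-free participants.** A reader might infer that the best responders are dropped or given an earlier attack's score, so that an effective drug is penalised. The documents do not support that. The carry-forward rule applies to missing variables, and a diary that reports no attacks is not a missing record. The diary's drop-down options (Figure 2) are not shown and may include zero. The stated SDs also make attack-free weeks rare, and slightly commoner in the reference arm.

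**ECG.** A reader might say that a normal-to-normal ECG has no valid score. It has one: the wording of *Marked effect* describes a change, so *Invalidation* is the more natural reading. What remains is an overlap of categories and some dilution of the comparison.

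**Conclusion.** The fault in the withdrawal rate stands. At participant level it is undefined for baseline non-users, whom eligibility does not exclude; it cannot score new use; and it is unbounded below. That conclusion needs no assumption about rates. Its size does: with 10% to 50% non-users, about 34 to 19 of 38 per arm are evaluable and the standard error rises by a factor of 1.05 to 1.41.

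The points on attack-free weeks and on normal-to-normal ECGs are requests for an explicit rule. They do not demonstrate bias against the drug. All of these are secondary outcomes, and the primary outcome, angina frequency, is unaffected. The changes should be made before unblinding, so that scoring rules are not chosen with the results in view.

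**What to change.** 1. **Emergency drugs.** Replace the rate as the tested outcome with weekly emergency-drug use at week 4, compared between arms and adjusted for baseline weekly use by a count model or ANCOVA. Report the percentage rate only descriptively, among baseline users. State the counting window for the before and after values, and how the two products are counted.
2. **Severity and duration.** State that an attack-free week scores 0 on both and is not treated as missing under the carry-forward rule.
3. **ECG.** State how a normal-to-normal ECG is classed, and report those participants separately.

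The cost is mainly wording in Section 2.8.1, Section 2.16 and Table 2. The printed formula already needs the before and after counts, so the new analysis requires no further quantity. Table 3 has no row for emergency-drug use, however, so the baseline count should be added there. If the two products are to be counted separately, the single diary item may have to be split. The small downside is that the result is less directly comparable with earlier studies that report the rate; the descriptive percentage covers part of that.

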### Exclusion criteria

2.4

Participants meeting any of the following criteria will be excluded from the trial.

(1)Patients who have previously experienced unstable angina pectoris and/or acute myocardial infarction; other diseases that may cause chest pain, such as congenital heart diseases, valvular diseases, and severe neurosis; arrhythmia; heart function of grade III or IV.(2)Acute stage of cerebral infarction.(3)Patients with severe liver- and/or kidney-related diseases; patients whose alanine aminotransferase and aspartate aminotransferase levels are higher than 1.5 times the upper limit of the normal range; patients with abnormal renal function.(4)Acute infection within the last 2 weeks.(5)Patients with other serious diseases that require treatment (like tumors, hematonosis, diabetes complications, etc).(6)Mental disorders or mental retardation which prevent the participant from completing the questionnaire.(7)Pregnant and lactating women.(8)Tendency to bleed; abnormal disseminated intravascular coagulation or international normalized ratio; low platelet levels.(9)Participation in other clinical trials within the last month.(10)Allergic constitution or allergy to the constituents of the drugs.(11)Unable to read or listen to the materials sent via WeChat (words, audio, and images).

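### Table 2 prints the T-wave limit for ECG efficacy as a maximum of 25%, beside ST limits that are minimums, so an isolated T-wave change can fit two grades or none

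*Protocol article*

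**What the plan says.** Section 2.8.1 of the Protocol article lists ECG efficacy among the secondary outcomes and bases its grading on a named set of evaluation criteria, set out in Table 2. The four rows are:

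- **Marked effect:** "The ECG returns to “substantially normal” or reaches “normal ECG".
- **Validation:** for the ST segment, "The decrease of ST segment is to increase by more than 0.05 mV after treatment, but it does not reach the normal level". For the T wave, "In the main electrocardiographic lead, the T wave changes lighter (up to 25" per cent). A flat T wave becoming upright, or improvement of a block, is also listed.
- **Invalidation:** "The ECG is basically the same as before treatment". No number is attached.
- **Aggravation:** for the ST segment, "The ST segment is to decrease by more than 0.05 mV after treatment". For the T wave, "In the main electrocardiographic lead, the T wave changes deeper (up to 25" per cent). An upright T wave turning flat or inverted, an ectopic rhythm and block are also listed.

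Section 2.16 treats ECG efficacy as ordinal data and assigns it the Kruskal–Wallis test. Nothing elsewhere in the article explains or corrects the 25% limit.

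**The concern.** Each of the two middle criteria contains an ST limit and a T-wave limit, and they point in opposite directions. The ST limit sets a floor: a shift must exceed 0.05 mV to count. The T-wave limit, as printed, sets a ceiling and no floor. A literal reader would therefore credit a barely visible T-wave change as response or worsening, and would have nowhere to put a substantial one that stops short of normal.

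A rank test on an ordinal scale needs every participant in exactly one grade. Where the printed rules give two grades or none, the ECG reader has to improvise, and two readers can grade the same pair of tracings differently. What is at stake is the reproducibility of one secondary outcome.

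**Working it through.** The plan gives no figure to reproduce here. The check is to apply the four rows of Table 2 to one kind of case.

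**Case tested.** A graded T-wave change of x% in the main lead, taken alone: no ST shift above 0.05 mV, no switch between flat, upright and inverted, no rhythm or block change, and no return to a normal or substantially normal ECG.

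**Inputs from Table 2.** Validation requires the T wave to be shallower by x ≤ 25%. Aggravation requires it to be deeper by x ≤ 25%. Invalidation requires an essentially unchanged ECG, with no numeric bound. Marked effect requires a normal or substantially normal ECG, which the case rules out.

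**Illustration (assumed starting value, not from the plan).** An inverted T wave of 0.20 mV, with x = |new depth − 0.20| / 0.20 × 100.

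- 0.19 mV: 0.01 / 0.20 = 5% shallower
- 0.21 mV: 0.01 / 0.20 = 5% deeper
- 0.16 mV: 0.04 / 0.20 = 20% shallower
- 0.10 mV: 0.10 / 0.20 = 50% shallower, still inverted
- 0.30 mV: 0.10 / 0.20 = 50% deeper

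| New depth | Change | 25% as a maximum (as printed) | 25% as a minimum, Invalidation as the remainder |
|---|---|---|---|
| 0.19 mV | 5% shallower | Validation, and also Invalidation | Invalidation |
| 0.21 mV | 5% deeper | Aggravation, and also Invalidation | Invalidation |
| 0.16 mV | 20% shallower | Validation; Invalidation too only if the reader calls it unchanged | Invalidation |
| 0.10 mV | 50% shallower | none | Validation |
| 0.30 mV | 50% deeper | none | Aggravation |

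The printed limit gives an overlap at the small end and a gap above 25%, in both directions. Read as a minimum, in line with the ST limits, and with Invalidation defined as the remainder, each of these cases falls into exactly one grade.

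**The case against.** The strongest reply is that this is loose English rather than a chosen rule. Table 2 renders a named external standard, its wording is rough elsewhere (the ST criterion for Validation speaks of a decrease that increases), and the ST limits beside the T-wave limits are minimums. The phrase may simply mean reaching 25%, and graders may work from the standard itself. That is plausible, and it is why the point should be treated as a wording error. It does not remove the point: the article prints the operative criteria, it does not say that the limit is a minimum, and the literal reading gives the opposite rule.

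A second reply is that a 5% change would in practice be called unchanged. At an assumed calibration of 10 mm per mV, 0.01 mV is 0.1 mm. This is fair for the smallest changes, but it leaves the gap above 25%.

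A reader might also infer more than the document supports:

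- **That every change up to 25% fits two grades.** The overlap is clear only for very small changes. A change of 20% to 25% need not count as essentially the same ECG.
- **That larger T-wave changes are never graded.** A change that normalises the ECG, makes one of the listed switches (flat to upright, upright to flat, upright to inverted) or comes with an ST shift above 0.05 mV still has a row.
- **That the arm comparison is pulled towards no difference.** Under double blinding, dilution is possible. The document gives neither the share of participants affected nor the rule readers would actually apply, so no size or direction can be claimed.
- **That the block criterion is lopsided because arrhythmia is excluded at entry.** Section 2.4 lists "congenital heart diseases, valvular diseases, and severe neurosis; arrhythmia; heart function of grade III or IV" without saying whether conduction block is covered, and a criterion that rarely applies misgrades nobody.
- **That worsening must take precedence when criteria conflict.** Table 2 does not say how its sentences combine, and a tie-break is detail that the full protocol may hold. Nothing here favours one tie-break over another.

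**Conclusion.** The point holds in a limited form. Table 2 states the T-wave limit as a maximum in both the Validation and the Aggravation row, against ST minimums in the same rows. For isolated graded T-wave changes the printed scale is neither exclusive (very small changes) nor exhaustive (changes above 25% that stay abnormal).

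This rests on reading the table as printed. The cited evaluation criteria are not at hand, so a minimum is inferred from consistency with the ST limits and not confirmed from the source. The number of participants affected cannot be estimated from the document.

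The consequence is confined to one secondary outcome. The primary outcome, angina frequency, and the sample size calculation in section 2.11 do not depend on it. It should be corrected because it is a wrong threshold in an operative outcome definition, but it does not threaten the trial's main conclusion.

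**What to change.** Make three changes to Table 2 before any ECG is graded:

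1. Check the table against the evaluation criteria it cites.
2. In both the Validation and the Aggravation row, restate the graded T-wave limit as a change of at least 25%, the reading consistent with the ST limits. In the Validation row, keep it short of normal, as the ST criterion already is, so that it does not run into Marked effect.
3. Define Invalidation as meeting none of the criteria in the other three rows.

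If the cited criteria turn out to say something different on the 25%, the table should follow them and state explicitly whether it is a floor or a ceiling, with grades that leave no gap.

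The cost is a wording change, with no extra recordings, readers or visits and no change to the planned test.
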